#### Patient-reported outcomes

*Patient general health assessment and pain visual analogue scales (VAS):* the patient is instructed to mark their ‘general state of health’ and ‘level of pain’ on two 100mm scales. The left end (0) corresponds to ‘very well’ and ‘no pain’ respectively, and the right end (100) to ‘extremely poor’ and ‘worst possible pain’ (100).

*The HAQ* assesses a patient’s level of functional ability. There are 20 questions in 8 categories of functioning that represent different activities - dressing, rising, eating, walking, hygiene, reach, grip and usual activities. For each item there is a 4-level difficulty scale scored from 0-3, representing no difficulty (0), some (1) or much (2) difficulty, and unable to do (3). The highest component score in each category determines the category score, unless the patient uses aids or devices for, or receives assistance with activities in that category, in which case the relevant category score is increased to 2 if the maximum score was previously <2. The 8 category scores are averaged into an overall score from zero to 3 [31].

*The RAQoL* consists of 30 statements derived directly from relevant patients, using, as far as possible, their own words. Respondents are required to indicate whether or not each of the statements applies to them; each affirmed statement contributes a score of 1 to the total score. Scores can range from 0 to 30 with a [32].

*The EQ5D* is a generic measure, which provides a single index value [33]. The scale includes a descriptive system, comprising 5 questions relating to different aspects of health each with 3 possible responses (‘no problems’, ‘some problems’ and ‘extreme problems’), and a visual analogue scale capturing the patient’s self-rated health where the endpoints are labelled ‘best imaginable health state’ and ‘worst imaginable health state’.

*The RA-WIS* [34] consists of 23 statements about the impact of the disease on working. Respondents are required to indicate whether or not each of the statements applies to them; each affirmed statement contributes with a score of 1 to the total score. Scores can range from 0 to 23; a score less than 10 indicate low work instability; scores in the range of 10-17 indicate moderate work instability; scores above 17 indicate high risk of work instability.

*Duration of early morning stiffness*; the patient is asked to estimate the time that elapsed between awakening and the time he/she is as flexible as he/she will be during a day involving typical activities. Duration in minutes is recorded up to a maximum of 720 min (12 h).

#### Imaging assessments

*MRI (high field gadolinium enhanced)* of the dominant hand and wrist (or alternative hand in the instance of greater clinical evidence of synovitis at baseline) will be performed at baseline, weeks 12, 24, 48 and 96. The dominant hand will be scanned unless the alternative hand has clinical evidence of greater synovitis at baseline. This study will use MRI to assess erosions, synovitis and bone marrow oedema using the accepted standard of RA magnetic resonance imaging score (RAMRIS), as well as direct synovial volume measurement and sensitive dynamic contrast enhanced magnetic resonance imaging (DCE-MRI) for quantification of synovitis and bone marrow oedema. Failure of MRI acquisition after baseline will not constitute a protocol violation and will not necessitate withdrawal from the study.

RAMRIS scoring system: scoring of erosions, synovitis and bone marrow oedema, using the validated outcome measures in RA clinical trials (OMERACT) system, will be performed by 2 independent, experienced scorers. The RAMRIS scoring system is a standardised, reliable, validated scoring system for synovitis, erosion and oedema. It has been successfully used to demonstrate response to treatment, including bDMARD [35]. Direct volume measurement of synovitis by manual segmentation will be performed. This will allow quantification of low volumes of synovitis not differentiated by RAMRIS scoring.

This will be followed by dynamic contrast enhanced (DCE)-MRI. Early enhancement rates measured from DCE-MRI depend strongly on synovial vascularity and capillary permeability and are therefore potentially better markers of inflammatory activity than simple volume measurements. DCE-MRI measurement of bone marrow oedema will also be performed.

A blinded assessor will perform *HRUS (Philips HDI 5000)* of the same hand and wrist as chosen for MRI at baseline, weeks 12, 24 and 48. If the target joint for synovial biopsy is at another site, the target joint will also be scanned. Images will be assessed for synovitis, using semi-quantitative scores of GS and PD and for presence or absence of erosions.

Plain radiographs of bilateral hands (carpal, MCP and PIP joints) will be performed at baseline, 12 and 24 months after the start of study medication to assess structural damage. Radiographs will be scored as per the modified Genant-modified Sharp scoring system [36].

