#### Secondary objectives

To assess the change in MRI synovitis between baseline and 48 weeks following very early ETN or MTX-TT regimen +/- delayed ETN.To evaluate other clinical efficacy endpoints at weeks 12, 24, 48 and 96 including:✓ Disease activity score-44 joint (DAS44) remission (DAS44 < 1.6), simplified disease activity index (SDAI), clinical disease activity index (CDAI), European League Against Rheumatism (EULAR) response criteria, American College of Rheumatology (ACR) response criteria.✓ Cumulative steroid dose.To evaluate patient-reported outcomes at weeks 12, 24, 48 and 96 including:✓ Physical function, assessed by the Health Assessment Questionnaire (HAQ), including normalisation of HAQ.✓ Quality of life scores assessed by RA Quality of Life (RA-QoL) and Euro QoL Five Dimensions (EQ-5D) questionnaires.✓ Work instability, assessed by RA Work Instability Score (RA-WIS) questionnaire.To evaluate imaging predictors of remission and sustained remission using:✓ High-resolution ultrasound (HRUS) at weeks 0, 12, 24 and 48 measuring grey scale (GS), PD and presence or absence of erosions.✓ Magnetic Resonance Imaging (MRI) at weeks 0, 12, 24 and 96 measuring synovitis and erosion scores.To evaluate other radiographic outcomes including:✓ Joint damage assessed by modified Sharp score of X-rays of hands and feet at weeks 48 and 96.

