### Patient eligibility

The target population are males and females, aged between 18 and 80 years, fulfilling the 2010 American College of Rheumatology/European League against Rheumatism (ACR/EULAR) RA classification criteria, who have not yet received DMARD therapy, with a maximum symptom duration of 12 months. Other criteria for inclusion are: patients with active RA at baseline (clinical evidence of synovitis and DAS28-ESR > 3.2) and positive anti-citrullinated peptide antibody (ACPA) or rheumatoid factor (RF) status. In the absence of RF and ACPA antibodies, patients are eligible for the study if they have evidence of power Doppler, a good indicator of active inflammatory pathology and predictor of structural damage. Power Doppler grade ≥1 in at least 1 joint on hand ultrasound is required (Table 1).

**Table 1 Tab1:** Eligibility criteria for randomisation into VEDERA trial

Inclusion Criteria
• Male and female patients aged between 18 and 80 years.
• Diagnosis of rheumatoid arthritis (new 2010 ACR/EULAR RA classification criteria).
• Symptom onset within the preceding 12 months.
• Patients with active RA at baseline: clinical evidence of synovitis (or imaging-evidence of synovitis in cases of uncertainty/subclinical disease) in hand and/or wrist joints evaluable by ultrasound and MRI, and DAS28-ESR > 3.2.
• Seropositivity for anti-citrullinated peptide antibody (ACPA) and/or rheumatoid factor. If ACPA and rheumatoid factor are both negative, presence of power Doppler (grade 1 or higher) in at least 1 joint on hand ultrasound is required.
• DMARD-naive (with the exception of previous exposure to hydroxycholorquine for an indication other than RA).
• All male and female subjects biologically capable of having children must agree to use a reliable method of contraception for the duration of the study and 24 weeks after the end of the study period. Acceptable methods of contraception are surgical sterilisation, oral, implantable or injectable hormonal methods, intrauterine devices or barrier contraceptives.
Exclusion Criteria
• Previous treatment with DMARDs for the management of RA.
• Intramuscular or intra-articular (of non-target joint) corticosteroid within 28 days of the screening visit; intra-articular steroid of the chosen target joint within 12 weeks of screening.
• Oral steroid of greater than 10mg prednisolone daily, or change in oral steroid dose within 28 days of study drug initiation at the baseline visit.

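### The rule for choosing the imaged hand looks only at clinical synovitis, although Table 1 admits patients on imaging-only synovitis with no side named

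*Protocol article*

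**What the plan says.** Three parts of the protocol article bear on this.

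- **Who may enter.** In Patient eligibility, Table 1 describes active disease as "clinical evidence of synovitis (or imaging-evidence of synovitis in cases of uncertainty/subclinical disease) in hand and/or wrist joints evaluable by ultrasound and MRI", together with a DAS28-ESR threshold. The running text of the same section gives only "patients with active RA at baseline (clinical evidence of synovitis and DAS28-ESR > 3.2" and does not mention the imaging alternative.
- **Which hand is imaged.** In Imaging assessments, the rule for MRI is "The dominant hand will be scanned unless the alternative hand has clinical evidence of greater synovitis at baseline". The section gives the rule twice, to the same effect. Ultrasound is done "of the same hand and wrist as chosen for MRI at baseline, weeks 12, 24 and 48". The one exception concerns ultrasound: "If the target joint for synovial biopsy is at another site, the target joint will also be scanned". The biopsy is optional.
- **What the images are for.** The first secondary objective is "To assess the change in MRI synovitis between baseline and 48 weeks". Under Other planned analyses, the RAMRIS score is treated as a secondary efficacy outcome, so it is formally tested. Ultrasound serves as a predictor of remission.

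**The concern.** The eligibility table and the hand rule use different evidence. Table 1 lets imaging stand in where examination is inconclusive. The hand rule lets only examination move the scan away from the dominant hand. In a patient whose synovitis is visible on imaging alone, examination may show no difference between the hands, so dominance decides. If the qualifying synovitis lies in the non-dominant hand, the endpoint is measured in the hand that did not qualify the patient.

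Baseline synovitis there may be close to zero, which leaves little room for improvement under either treatment. That sits badly with the protocol's own reason for imaging, given in the Background and the Discussion, which is that clinical scores can be insensitive. What is at stake is the precision of the MRI synovitis comparison and the usefulness of the ultrasound measures.

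**Working it through.** No figure in the protocol bears on this point, so the main check sets the rules side by side.

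1. **Imaging-only entry is possible.** Table 1 allows it in uncertain or subclinical cases.
2. **The qualifying joint can be on either side, as far as the wording goes.** Table 1 names hand and/or wrist joints and no side.
3. **The hand rule has one disease-based override.** Dominance is the default, and greater clinical synovitis in the other hand is the only thing that displaces it.
4. **Result for the patient in question.** With imaging-only synovitis in the non-dominant hand and no clinical difference, the override is not met. The dominant hand is imaged by MRI at baseline and weeks 12, 24, 48 and 96, and by ultrasound at baseline and weeks 12, 24 and 48.
5. **Exceptions.** A biopsy target joint elsewhere gets an added ultrasound. MRI has no exception.

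**Illustration of size (assumed inputs).** The protocol gives neither the share f of such patients nor an MRI effect size. Its 80 % power is for DAS28 remission. Assume 60 × 0.9 = 54 evaluable patients per arm and a standardised MRI effect that would give 80 % power at the two-sided 5 % level:

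d = (1.960 + 0.842) × √(2/54) = 0.54.

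Assume also that a share f in each arm shows zero change. The mean difference shrinks to (1 − f) of its value.

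- *SD unchanged:* power = Φ((1 − f) × 2.802 − 1.960).
- *SD also shrinks:* patients with zero change add no spread of their own. If the mean change is small relative to the SD, the variance falls by about (1 − f), and power = Φ(√(1 − f) × 2.802 − 1.960).

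| f (assumed) | Power, SD unchanged | Power, SD shrinks |
|---|---|---|
| 2 % | 78 % | 79 % |
| 5 % | 76 % | 78 % |
| 10 % | 71 % | 76 % |
| 20 % | 61 % | 71 % |

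Zero change is itself a worst case, because the dominant hand may also carry some synovitis.

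**The case against.** The strongest reply is that few patients can be affected. Several conditions must hold together: synovitis seen on imaging only, located in the non-dominant hand, no clinical difference between hands, and little synovitis in the dominant hand even on contrast-enhanced MRI. The Background describes RA as symmetrical, and nothing in the protocol suggests a share as high as 10 or 20 %. This stands, and it limits the size of the point.

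Second, the requirement that the joints be evaluable by ultrasound and MRI could be read as tying the qualifying synovitis to the hand that will be scanned. That reading is possible, but the text does not say so, and one clause would settle it.

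Third, the difference between the running text and Table 1 may be mere condensation, since the text refers to the table. That is plausible. Even so, the text states clinical synovitis as the criterion without hinting at an alternative, and aligning the two costs nothing.

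Some stronger readings are tempting but unsupported:

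- *A reader might infer that the seronegative criterion is a second way in without clinical synovitis.* It is not. Table 1's "presence of power Doppler (grade 1 or higher) in at least 1 joint on hand ultrasound is required" replaces missing antibodies. It is a separate item that applies in addition to the synovitis item.
- *A reader might infer that the qualifying joint is never followed.* Clinical joint counts continue to week 96, radiographs cover both hands, and a biopsy target joint elsewhere is scanned by ultrasound. The gap is in MRI and, outside the biopsy exception, in ultrasound.
- *A reader might infer that such patients would be wrongly counted as in imaging remission.* The protocol defines no such endpoint. Its remission thresholds are for DAS28, DAS44, CDAI and SDAI.

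**Conclusion.** The mismatch is real, and it comes from a definite rule in the article rather than from detail left to a fuller document. Its consequence is modest: reduced sensitivity of secondary imaging outcomes in a subgroup whose share is unknown and probably small.

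A reader might take it as a source of bias between the arms. The documents do not support that, because the hand is chosen on baseline status and the loss is expected equally in both arms. The DAS28 primary endpoint does not depend on the imaged hand.

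The power figures only illustrate scale. They assume the affected share, an MRI comparison with 80 % power and zero change in the affected patients. The conclusion also rests on reading Table 1 as allowing either side, since it names none. The point is worth acting on because the correction is so cheap.

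**What to change.** In Imaging assessments, add one sentence: where inclusion rested on imaging evidence of synovitis and the hands do not differ clinically, the hand with the qualifying imaging synovitis is scanned, with the dominant hand as tie-break. Alternatively, state in Table 1 that the qualifying synovitis must lie in the hand to be scanned. In either case, reconcile the running text of Patient eligibility with Table 1 on whether imaging evidence is enough.

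The cost is protocol wording. In these few patients the choice of hand would depend on the screening image, which already exists, so no extra scan is needed. The rule should stay this narrow. Using ultrasound to choose the hand in every patient whose hands look clinically equal could require added scans of both hands, because the protocol does not require an eligibility ultrasound for seropositive patients with clinical synovitis and does not say that the eligibility ultrasound covers both hands.

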#### Exploratory biosample based research

Blood samples will be collected at baseline and weeks 12, 24, 36, 48, 96, at time of early discontinuation (if indicated) and at time of flare (if indicated). This will include collection of serum, plasma and heparinised blood (for flow cytometry and functional studies).

Synovial biopsy (optional) will be taken from a target joint: an active joint (identified at baseline by presence of PD activity on ultrasound) or alternatively, if necessary, a clinically uninvolved, accessible joint may be chosen. The optional biopsy will be acquired via arthroscopy or under ultrasound guidance at baseline and week 24; at week 48 in patients randomised to treatment arm 2 receiving delayed ETN from week 24, and at time of flare in the case of loss of response in an initial responder. Failure of biopsy acquisition at any time point will not constitute a protocol violation and will not necessitate withdrawal from the study.

The sample collection will be used for wide-ranging studies including cellular phenotyping, soluble biomarker evaluation and gene expression studies.

A detailed study schedule is provided in Table 3.

**Table 3 Tab3:** Study schedule

				Arm 2^a^		Arm 2^a^	Arm 2^a^								
Study Week	Weeks -4 to 0	Week 0	Week 4	Week 8	Week 12	Week 16	Week 20	Week 24	Week 36	Week 48	Week 60	Week 72	Week 84	Week 96	Early discontinuation
Study Phase	Screen	Baseline	Safety visit							1^0^ Endpoint				End of Study	
Visit No.	1	2	3	4	5	6	7	8	9	10	11	12	13	14	
Informed Consent (patient information will be provided > 24 hrs prior to screen)	X														
Inclusion/exclusion criteria	X	X													
Randomisation		X													
Demographics, RA Hx, past medical Hx, Family Hx, CV risk factors^b^	X														
Physical examination^c^	X				X										X
Vital signs^d^	X	X	X		X			X	X	X	X	X	X	X	X
Pregnancy test^e^	X	X													
ESR, CRP and HS-CRP	X	X	X (Arm 2 only)	X	X	X	X	X	X	X	X	X	X	X	X
Blood chemistry, haematology	X	X	X	X	X	X	X	X	X	X	X	X	X	X	X
Urinalysis	X	X	X		X			X		X		X		X	X
Serology: RF, ACPA and ANA	X													X	X
ECG	X														
Chest x-ray/TB test^f^	X														
Hepatitis (B and C) serology	X														
VAS assessments: patient general health, patient global, patient pain	X	X	X (Arm 2 only)	X	X	X	X	X	X	X	X	X	X	X	X
Physician VAS global disease activity	X	X			X			X		X		X		X	X
DAS_28/44_ joint assessment^g^	X	X	X (Arm 2 only)	X	X	X	X	X	X	X	X	X	X	X	X
Early morning stiffness, HAQ, RA QoL, EQ-5D, RA-WIS		X			X			X		X		X		X	X

a. Visits at weeks 8, 16 and 20 are only applicable to patients in treatment arm 2. b. Cardiovascular risk factors include: smoking habit (pack years), alcohol intake (units/week), amount of exercise taken, dietary intake (days/week ≥ 5 portions fruit or vegetables consumed), and family history of premature cardiovascular disease age <55 years. c. Physical examination Includes height and body weight at screening. d. Blood pressure after a 5-min rest, pulse rate and body temperature e. Urinary pregnancy test for women of child bearing potential only f. Chest x-ray, if not already performed within 24 weeks prior to the study. TB testing includes TB Gold Quantiferon +/- T spot test +/- Mantoux test. g. Whenever possible, joint assessments should be performed by the same blinded assessor throughout the time course of the study to reduce potential investigator bias

### Follow-up

At study completion (96 weeks), patients will be invited to take part in the Inflammatory Arthritis Continuum (IACON) study. This is an in-house, prospective, longitudinal, observational study of patients with inflammatory arthritis, with ethical approval to obtain blood samples and clinical and imaging data in consenting patients. Inclusion of all patients with inflammatory arthritis in IACON will allow recording of longer-term outcomes such as sustained response and drug-free remission permitting future observational work.

### Statistical considerations

#### Sample size

Clinical remission (DAS28 remission) forms the basis of the primary outcome. The COMET study, reported remission rates in patients with very early RA (less than 4 months since diagnosis) treated with both ETN and MTX or MTX monotherapy of 70 % versus 35 % respectively. In patients with disease duration of less than 2 years but greater than 4 months, treatment with ETN and MTX was associated with 48 % remission rate. In the COMET study patients in the very early RA group were recruited within 4 months of RA diagnosis, using ACR 1987 criteria. In contrast, VEDERA will recruit patients within 12 months of symptom onset. Whilst all patients will meet RA criteria at the point of recruitment, ACR/EULAR 2010 criteria are being used, which identify patients at an earlier stage of the disease course than the 1987 criteria, and patients can potentially be recruited concurrently with diagnosis. It is likely that patients recruited to VEDERA will be at a similar stage in their disease course to the patients in the very early RA group in COMET, potentially an even earlier stage.

To account for the possibility that the interval between the treatment groups may not be as large as that seen in COMET a 30 % difference has been used as a basis for the sample size calculation. Assuming therefore that patients in treatment arm 1 are likely to achieve up to 70 % remission, and treatment arm 2 approximately 40 % remission; for 80 % power at the 5 % significance level and allowing for a 10 % dropout rate, at least 49 patients per arm will be required. Increasing this to 60 per arm would allow for a subgroup analysis of treatment arm 2 patients that proceed to require delayed ETN and MTX to be compared with treatment arm 1 and indeed those in arm 2 that stay on conventional therapy. This is an exploratory analysis; we estimate that 50 % of treatment arm 2 patients will require delayed ETN and MTX. With roughly 30 patients in each subgroup of treatment arm 2 we will obtain sufficiently accurate estimates of remission rates.

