### Randomisation

Once eligibility is confirmed and all relevant procedures have been completed, participants will be block randomised 1:1 to one of the following two treatment groups (Fig. 1):Treatment Arm 1 or ‘very early ETN’ will receive ETN and MTX combination therapy administered for a total duration of 48 weeks.Treatment Arm 2 or ‘delayed ETN’ will receive initial MTX monotherapy with adoption of a TT protocol (standard care involving monthly DAS28-ESR assessment with escalation to combination sDMARD therapy if not achieving LDA at, or after, 8 weeks) and step-up to ETN and MTX at 24 weeks if failing to achieve clinical remission.

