#### Analyses

Descriptive summary statistics will be provided for all variables at baseline and at each visit at which the variable is assessed. For continuous variables the following information will be provided: number of patients (N), mean, standard deviation, minimum, median, maximum and 25 % and 75 % quartiles. For categorical data frequency (absolute and relative) distributions will be provided. Differences between groups will be summarized according to data type and 95 % confidence intervals around these estimates will be constructed.

All inferential analyses will be conducted using two-tailed tests at the 5 % level of significance. The Holm correction (modified Bonferroni) will be employed on a family-wise basis to control for multiple comparisons of secondary outcomes.

Complete details of statistical analyses and methods, including data handling conventions, will be contained in a separate statistical analysis plan which will be finalized before the database is locked.

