## Discussion

This pragmatic, randomised phase IV, open-label study is comparing first line ETN and MTX combination therapy with a TT regimen starting with MTX monotherapy regimen with sDMARD escalation followed by ETN and MTX at week 24 if the treatment target of remission (or LDA with physician impression of remission) is not achieved.

The fundamental objective of this study is to determine whether TNFi instituted as first-line therapy in early RA confers better outcomes (including depth of remission and exploratory parameters indicating normalisation of immune system aberration) compared to a conventional TT therapeutic approach with delayed TNFi if required. The VEDERA study will contribute to the existing evidence [37, 38] and in addition addresses the question of whether quality of response to TNFi following MTX-failure differs from that achieved with first-line use, prior to MTX exposure. The accurate imaging aligned with the clinical assessments will also ensure correct categorisation of patient response, to address the weaknesses of clinical composite measures for assessing remission [39].

Although the planned sample size (*n*=120) is relatively small, the study is adequately powered to detect a clinically meaningful difference in remission rate, based on existing published data. Secondary outcomes are expected to be correlated with the primary outcome and we therefore anticipate the effect size to be similar for these variables, which are considered supportive of the primary hypothesis. For exploratory endpoints the focus will be purely descriptive; the sample size has been inflated to help ensure that planned subgroup analyses of patients receiving delayed ETN will include sufficient patients, based on rules of thumb for pilot studies.

One of the secondary objectives of the study is remission maintenance and sustainability after ETN withdrawal. There is increasing published data regarding this [40], and while this study does not primarily seek to investigate drug tapering following remission, it will provide additional insights. Finally, the biosamples collected will allow investigation of the pathobiology of disease, mechanisms of drug action and predictors of response and remission in order to enable more effective tailoring of therapy in clinical practice.

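### The 40 % arm 2 remission rate behind the stated power is hard to square with the plan's own forecast that only half of arm 2 will need etanercept

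*Protocol article*

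**What the plan says.** The primary endpoint is DAS28 remission at week 48 (Primary objective; Sample size). The planning rates are that "treatment arm 1 are likely to achieve up to 70 % remission, and treatment arm 2 approximately 40 % remission", and "a 30 % difference has been used as a basis for the sample size calculation". The source given is the COMET trial: 70 % on etanercept plus methotrexate against 35 % on methotrexate monotherapy in very early disease. The calculation is made "for 80 % power at the 5 % significance level", and, "allowing for a 10 % dropout rate, at least 49 patients per arm will be required". The number is then raised to 60 per arm, for subgroup estimates within arm 2.

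For those subgroups the same paragraph says "we estimate that 50 % of treatment arm 2 patients will require delayed ETN and MTX", giving about 30 patients in each half of the arm. The Randomisation section defines who needs it: "step-up to ETN and MTX at 24 weeks if failing to achieve clinical remission". Table 2 and the Treatment arm two section apply the same rule, with DAS28-ESR of 2.6 or more as the trigger. The endpoint uses the same cut-off (Clinical efficacy section). Before week 24, arm 2 patients who miss low disease activity also have sulfasalazine and hydroxychloroquine added.

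The Discussion concludes that "the study is adequately powered to detect a clinically meaningful difference in remission rate, based on existing published data". It also describes the step-up target more loosely, letting a patient in low disease activity whom the physician judges to be in remission count as having met it.

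**The concern.** The arm 2 rate looks borrowed from a different comparator. The only control figure cited is for methotrexate alone. Arm 2 escalates from week 8 and gives etanercept from week 24 to patients who have not remitted, so its week-48 rate should reflect that strategy.

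The plan's own switch forecast points the same way. If half of arm 2 does not need etanercept, and the rule for needing it is absence of remission at week 24, then about half is expected to be in remission before any etanercept is given. The other half then has 24 weeks on etanercept plus methotrexate before the endpoint. A planning value of 40 % lies below that starting point.

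At stake is how a non-significant primary result is read. The Discussion says the trial is adequately powered, and readers will rely on that. If arm 2 does materially better than 40 %, power is well below the stated 80 %, and a null result says less than the claim suggests.

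**Working it through.** **Inputs.** Arm 1 70 %; arm 2 40 %; power 80 %; two-sided 5 % (Analyses section: "All inferential analyses will be conducted using two-tailed tests at the 5 % level of significance"); 1:1 allocation; Pearson chi-squared test; 10 % dropout; 60 per arm planned; 50 % of arm 2 stepping up.

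**1. The plan's own figure.** Pooled-variance formula, with p̄ the mean of the two rates:

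n = [1.96·√(2p̄(1−p̄)) + 0.842·√(p1(1−p1) + p2(1−p2))]² / (p1−p2)²

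With p1 = 0.70, p2 = 0.40, p̄ = 0.55: n = (1.379 + 0.565)² / 0.09 = 42 per arm, and 42 / 0.9 = 47 after dropout. The stated 49 is within two patients of this. With 44 evaluable patients per arm (49 less 10 %), power is 82 %. The calculation is sound for its inputs, so the issue is the arm 2 input.

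**2. What 40 % at week 48 requires.** Let k be the share of week-24 remitters still in remission at week 48, and s the remission rate at week 48 among those stepped up. The documents give neither, so both are assumptions. Taking the forecast and the Methods rule at face value:

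arm 2 rate = 0.5k + 0.5s, so 40 % requires k + s = 0.80.

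| s (switchers in remission) | k needed for 40 % | week-24 remitters who must lose remission |
|---|---|---|
| 0 | 0.80 | 20 % |
| 0.20 | 0.60 | 40 % |
| 0.35 | 0.45 | 55 % |

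In each row the arm goes from 50 % at week 24 to 40 % at week 48, a net fall after the step-up.

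**3. Allowing for the exception in the Discussion.** Suppose half the arm still switches, but some of the other half are in accepted low disease activity and none of these remits by week 48 (assumption).
- 45 % in true remission at week 24, k = 0.8: 0.45 × 0.8 = 36 %. The remaining 4 points must come from switchers, so s = 0.04 / 0.5 = 8 %.
- 40 % in true remission, k = 0.7: 0.40 × 0.7 = 28 %. The remaining 12 points give s = 0.12 / 0.5 = 24 %.

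The second case is not absurd, but the arm still gains nothing between weeks 24 and 48.

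**4. Power by arm 2 rate.** Arm 1 is held at 70 %:

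Power = Φ{[|p1−p2|·√n − 1.96·√(2p̄(1−p̄))] / √(p1(1−p1) + p2(1−p2))}

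Example, p2 = 0.50, n = 60: (0.20 × 7.746 − 1.358) / 0.678 = 0.28, so power is 61 %.

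| Arm 2 at week 48 | 54 per arm (60 less 10 %) | 60 per arm | Example k, s (50 % switching) |
|---|---|---|---|
| 40 % | 89 % | 92 % | 0.5, 0.3 |
| 45 % | 76 % | 80 % | 0.6, 0.3 |
| 50 % | 57 % | 61 % | 0.7, 0.3 |
| 55 % | 36 % | 40 % | 0.8, 0.3 |
| 60 % | 19 % | 21 % | 0.8, 0.4 |

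Power of 80 % is reached up to an arm 2 rate of 43.6 % with 54 per arm and 45.0 % with 60. The smallest difference detectable at 80 % power is therefore 70 − 43.6 = 26.4 points, or 70 − 45.0 = 25.0 points.

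**The case against.** Several points on the other side have force.

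- **Different weeks.** A reader might infer a flat contradiction between 50 % and 40 %. The documents do not support that: one figure concerns week 24 and the other week 48, and relapse among remitters could bring the second below the first. What stands is that the plan never says it expects this.
- **The exception in the Discussion.** It means fewer than 50 % may be in DAS28 remission at week 24. This narrows the gap, as step 3 of the working shows, but does not close it. The exception is also absent from the Randomisation section, Table 2 and the Treatment arm two section.
- **Purpose of the 50 %.** It is a rough estimate offered for an exploratory subgroup analysis and is not an input to the power calculation. That limits its precision, but it still describes the same arm, and the step-up rule ties it to the primary endpoint's definition.
- **Existing reserve.** The plan narrowed COMET's 35-point gap to 30 and enrols 60 per arm rather than 49. This covers an arm 2 rate up to about 45 % without dropout, and not 50 %.
- **The Discussion sentence.** Read as a statement about detecting 30 points, it is correct, with 89 to 92 % power. The planned 95 % confidence intervals also limit misreading of a null result. But the sentence bases adequacy on published data, and the control figure cited is for monotherapy.

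A reader might also put COMET's 48 % (etanercept plus methotrexate in disease of more than 4 months and less than 2 years) in for the switchers. With k = 0.8 that gives 0.5 × 0.8 + 0.5 × 0.48 = 64 % and power of about 10 %. The plan does not describe those patients as having failed earlier treatment, whereas arm 2 switchers are selected for not having remitted. That scenario is only an assumption and should not be presented as the plan's own figure.

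**Conclusion.** The point holds as a fault in a planning assumption and in the power stated from it. It is not an arithmetic error, since 49 per arm is reproduced closely enough. A 40 % week-48 rate in arm 2 fits the plan's switch forecast only if remission in the arm falls, or gains almost nothing, after step-up, and no section states or justifies that. If arm 2 merely holds 50 %, power is 57 to 61 %; at 55 % it is 36 to 40 %.

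These figures are exact for the rates shown, but which rate applies depends on k and s, which the documents do not give. It therefore cannot be said that the trial has any one particular lower power. Arm 1 is held at 70 %, which the plan words as an upper limit; for a given arm 2 rate below it, a lower arm 1 rate would shrink the difference further.

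**What to change.** Keep 120 patients, the endpoint and the test. In the Sample size section:

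- Replace the 40 % with a week-48 arm 2 rate built from the 50 % switch forecast, stating the assumed persistence of remission and the assumed remission rate after step-up.
- Restate power at 60 per arm, and at 54 after dropout, over arm 2 rates of about 40 to 60 %.
- State the smallest difference detectable at 80 % power with arm 1 at 70 %: about 25 to 26 points.

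In the Discussion, tie the adequacy claim to that detectable difference. Reconcile the step-up target described there with the Randomisation section, Table 2 and the Treatment arm two section, because the forecast week-24 remission share depends on which one applies.

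The cost is rewording and a less favourable stated power. No extra patients are needed.
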